### Control and Intervention

The control group will receive usual antenatal maternity care with the addition of a written nutrition and weight gain resource: the booklet “Good nutrition in pregnancy,” published by the ACT Government. Usual care for women includes attendance at antenatal appointments in accordance with the following gestation schedule: 12-14 weeks (booking visit), 16, 20, 26, 30, 33, 36, 38, 40, and 41 weeks. Women choosing shared care usually alternate visits with their general practitioner and hospital clinic. Although women’s BMI is calculated at their first hospital-booking visit, weighing is not routinely attended at subsequent antenatal clinic appointments or at labor commencement. Advice on weight gain is ad hoc, and dietary advice is focused on food safety in pregnancy. Women with a BMI over 35 kg/m^2^ are referred to a community dietitian. Some amendment to usual care will be required to weigh women at 38 weeks and at commencement of labor.

The intervention group will receive usual care as outlined above and will also be provided access to the Eating4Two smartphone app at no cost. The app, password protected, will be able to be downloaded from App stores. The app provides dietary information appropriate to pregnancy and advice on good nutrition (drawn from the Australian Dietary Guidelines 2017 [23]), managing common pregnancy-related symptoms (such as heart burn), and GWG. Photographs are included that demonstrate serving sizes for relevant food groups. The woman’s weight is graphed against the range recommended by the IOM for their starting BMI and records this information, making it available for the researchers. When weight gain is above or below the recommended range, women are prompted to discuss the issue with their maternity caregiver so that individual advice can be provided. The app also sends regular messages to the participant (specific to their gestation) with information about their baby’s growth, development and nutritional needs, motivational messages, tips on weight management and physical activity in pregnancy, and reminders to discuss weight gain with their maternity caregivers. The aim of the app is to augment usual antenatal care by providing information to women about nutrition, empowering them to monitor their GWG, and encouraging discussion of weight between women and their maternity caregivers when GWG deviates from the recommended levels.

### Data Collection

The weight of all women will be established prepregnancy (self-reported), pregnancy (at enrolment in study <15 weeks gestation, self-reported), at approximately 38 weeks gestation (measured), commencement of labor (measured), and at 6 months postpartum (self-reported). The weight of women in the intervention group as recorded by the women in the app will also be available to researchers. Routinely collected clinical maternity data will be used where possible and this will be drawn from clinical records. This includes demographic data (age, parity, ethnicity and address) and behaviors including smoking and clinical outcomes. Using geo-coding, addresses of women participating in this study will be matched to the Australian Bureau of Statistics geographical data and allocated an IRSAD score. Data not collected routinely (including education and marital status) will be sought from participants (via a questionnaire), which will include participation in exercise and dietary intake established at baseline and repeated at approximately 38 weeks gestation, information about the GWG resources and advice accessed by women (38 weeks) and their rating of the app (38 weeks for intervention group only). Satisfaction with perinatal care will be assessed by questionnaire at 4-6 weeks postpartum.

The primary outcome will be GWG, specifically the proportion of women whose GWG falls within the range recommended for them by the IOM for their baseline BMI. GWG will be calculated by subtracting the woman’s first recorded pregnancy weight from her recorded weight in labor. Secondary outcomes including pregnancy complications, labor interventions, mode of birth, and neonatal outcomes will be drawn from routinely collected maternity outcome data and will include the following data: complications arising in pregnancy including hypertension and gestational diabetes (as diagnosed by health professional), labor interventions (including induction or augmentation of labor), mode of birth (spontaneous vaginal, assisted vaginal, caesarean section), birth complications (eg, shoulder dystocia), and neonatal outcomes (including gestation, birth weight, admission to neonatal nursery, Apgar score).

Women allocated to the intervention group will be required to enter the following initial data into the Eating4Two app: height, prepregnancy weight, and baby’s due date. Thereafter, they will be requested to enter their weight on a weekly basis. Data transferred to the researchers directly from the app include height, prepregnancy weight, baby’s due date, and weekly weights. Four to six weeks after the participant’s due date, they will be sent an email containing a link to a Web-based questionnaire in Qualtrics assessing quality of perinatal care. The Quality Perinatal Care Questionnaire is a 46-item instrument with 6 validated subscales originally developed in Canada and validated in an Australian population [42]. This email will also contain an invitation to participate in a focus group or individual interview. This component seeks to understand the barriers and facilitators to optimal GWG in pregnancy from a personal, social, and health care perspective, and specifically to understand how these may differ for women of different prepregnancy BMI and IRSAD (index of relative social advantage and disadvantage) groups. Those in the intervention group will also be asked specific questions about the app, which will provide additional information on the components of the App and its acceptability, functionality, engagement, and motivational capacity.

Additionally, this seeks to explore how BMI and IRSAD might impact app evaluation. Focus groups will aim for between 8 to 12 participants in each session, and intervention and control group women will attend separate groups. We will also attempt to group women living in areas with similar IRSAD scores and prepregnancy BMI categories together so that we can examine the ways in which these factors might impact issues relating to gestational weight management, engagement with maternity care providers, and engagement with the Eating4Two app(for those in intervention group). We will aim for 8 focus groups in total (64-96 participants). Individual interviews (by phone) will be offered to those who cannot attend focus groups.

It can be difficult for new mothers to attend scheduled focus groups, and individual phone interviews offer greater flexibility. We will aim for a total of 20 individual interviews balanced between intervention and control groups and sites. All focus groups and interviews will be audio recorded and transcribed verbatim.

### Data Analysis

Primary analysis will be conducted with the researcher responsible for analysis blinded to group allocation. An intention-to-treat analysis will be conducted including withdrawals and losses to follow-up. Although even distribution of baseline characteristics between the intervention and the control groups is expected due to randomization, this will be further assessed by Chi-squared test and Student *t*-test for categorical and continuous variables, respectively. Descriptive statistics for all outcome variables will be calculated before statistical analysis. Continuous outcome variables will be evaluated for normality and transformations will be applied as necessary. Regression analysis with adjustments for confounding variables (prepregnancy BMI, smoking, IRSAD score, parity, age) will be used to evaluate the primary outcome and relative risk, and its 95% CIs will be calculated. Significance will be set at .05. The multiple imputation method will be used to generate possible values for missing values. This is considered gold standard for dealing with missing data. Data will be analyzed in IBM SPSS Statistics).

Qualitative data analysis will firstly follow a simple descriptive approach using NVIVO 11 software (QRS International). Qualitative descriptive analysis is a low-inference analysis that uses an inductive approach to develop descriptive themes. All transcripts will be coded by first attaching a descriptive label to each meaning unit (a sentence or group of sentences conveying a message or concept relevant to the study); first level. Descriptive labels will be examined and grouped with other labels conveying a similar idea to create descriptive themes; second level. Data will be analyzed within groupings (BMI and IRSAD) and then compared across groups; third level. This will be attended by 2 researchers independently (first level) and then collaboratively on the second and third levels of analyses.

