### Settings

The proposed study will be implemented in 3 geographic regions. Region 1 is the Australian Capital Territory (ACT) and will include women attending the Centenary Hospital for Women and Children (a tertiary-level hospital) and Calvary Hospital (a sub-acute facility). These hospitals facilitate over 5000 births per annum [39]. Region 2 is the Hunter New England region of NSW, Australia, and will include women attending the John Hunter (a tertiary-level hospital) and Maitland (a sub-acute facility) hospitals. These hospitals facilitate approximately 5700 births per annum [40]. Region 3 is Port Macquarie-Hastings and includes women attending Port Macquarie Base Hospital (a sub-acute facility) that facilitates approximately 2000 births per annum.

The index of relative socioeconomic advantage and disadvantage, developed by the Australian Bureau of Statistics draws on census data to describe the economic and social conditions of people and households in a geographical area, the smallest area being a Statistical Area 1 (SA1), which includes approximately 400 people. A low score reflects greater disadvantage and a high score greater advantage [41]. The ACT as a whole, has an IRSAD decile ranking of 10 though individual suburbs range in decile rankings from 7-10. The Newcastle local government area (in which the John Hunter and Maitland Hospitals are situated) has a ranking of 7 and draws on areas with rankings that range from 3 to 7; Port Macquarie has a ranking of 5, drawing on areas with rankings ranging from 1 to 10.

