### Recruitment and Randomization

Recruitment will be via social media and health professionals providing antenatal care or childbirth education. Social media will publish the research aims and eligibility criteria and invite potential participants to contact the research assistant who will provide more information and a research information pack. Health professionals will introduce the study to potential participants and provide those interested and eligible with a research information pack. They will also collect contact details of those expressing an interest (for follow up by the research assistant). The research information pack contains a concise lay description of the study, contact details of the researchers, a hard copy questionnaire to establish baseline demographic details, consent form, and reply-paid envelope. The research assistant will contact all those provided with an information pack to discuss potential participation and answer any questions they may have. Those who agree to participate will complete the consent form and questionnaire and return these to the research coordinator in the reply-paid envelope provided. The research coordinator will record the date of receipt.

The research coordinator will randomize participants on receipt of the signed consent form. Participants will be randomized using a 1:1 ratio in balanced blocks and stratified by BMI and geographical setting. Allocation concealment will be assured through the use of a remote Web-based allocation service.

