## Discussion

### Principal Findings

This protocol aims to determine whether the use of the smartphone app Eating4Two is effective in assisting women to optimize GWG and improve birth outcomes. The intervention takes advantage of smartphone technology, addresses the problem of the limited health service resources available to meet an expanding area of need, and focuses on empowering women to manage their weight in partnership with their maternity care provider. In addition, it addressed the question of whether the intervention impacts differently women with varying levels of relative socioeconomic advantage and disadvantage.

Our feasibility study clearly identified problems in both the recruitment strategy and in the app platform. Although iOS (iPhones) is more popular with younger populations [48], both the Android and iOS providers dominate the field in Australia, and providing the app in both platforms will greatly increase study eligibility.

The recruitment strategy was also revised to involve a range of maternity care service providers including general practitioners, private obstetricians, employed obstetricians, and midwives. Most women visit their general practitioner to confirm their pregnancy, and this makes this group particularly important to ensure that women are recruited early to resolve the other main issue compromising eligibility of advanced gestation. Relying on clinicians can be a risky recruitment strategy as they are often busy and prioritize clinical care. There are, however, a number of strategies that will be employed to enhance the strategy including early engagement; study logo; and regular communication through a study newsletter, eg, acknowledging participation (with merit letters or certificates for example) and showing appreciation [49].

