### Limitations

The study relies on self-reported height and weight to establish the BMI of participants in the intervention group. Maternity care providers usually calculate BMI at the first antenatal booking visit, and participants can correct these data within the application if necessary. Nonetheless, it is reliant on the accuracy of the participant’s entry. Total weight gain is established by subtracting the woman’s first recorded pregnancy weight from her recorded weight in labor, and we will be unable to vouch for the accuracy of the scales used in various antenatal and labor and birth settings. The quality of the scales used and the procedures for maintaining and calibrating them may vary. Although this may affect the results of the study, it is important to test methods that will be used in translating the intervention to service delivery if successful. Finally, this study does not include any follow-up of women to assess their longer-term weight change post birth.

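### The primary regression adjusts for one of the two randomisation strata: BMI is in the covariate list, geographical setting is not

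*Protocol article*

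**What the plan says.** Recruitment and Randomization sets the design: "Participants will be randomized using a 1:1 ratio in balanced blocks and stratified by BMI and geographical setting". I take geographical setting to mean region, since Settings states: "The proposed study will be implemented in 3 geographic regions".

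Data Analysis names the adjustment set for the primary outcome: "Regression analysis with adjustments for confounding variables (prepregnancy BMI, smoking, IRSAD score, parity, age) will be used to evaluate the primary outcome". The bracketed list has five entries and nothing marks it as a set of examples. Region, hospital and site are not in it, and no interaction term is mentioned.

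On IRSAD, Data Collection says: "addresses of women participating in this study will be matched to the Australian Bureau of Statistics geographical data and allocated an IRSAD score". Settings gives the spread of decile rankings in each region. For the third it says: "Port Macquarie has a ranking of 5, drawing on areas with rankings ranging from 1 to 10".

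In the Discussion, Principal Findings says the protocol takes up the question of "whether the intervention impacts differently women with varying levels of relative socioeconomic advantage and disadvantage".

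**The concern.** When allocation is balanced within strata, part of the outcome variation, the part between strata, is removed from the comparison of the arms by design. A model without the stratifying factor still counts that part as noise. Its standard error is then somewhat too large and some of the precision bought by stratifying is lost. BMI is handled correctly here and region is not.

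IRSAD might seem to do region's work, because the regions were chosen to differ in socioeconomic position. If it did, the omission would not matter.

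The second, smaller matter is a mismatch between a claim and an analysis. A covariate entered only as a main effect shifts the outcome level equally in both arms. It says nothing about whether the app works better for some women than for others.

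**Working it through.** **1. Strata against covariates.** Strata: BMI, geographical setting. Covariates: BMI, smoking, IRSAD, parity, age. One of the two strata is missing.

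**2. Can IRSAD stand in for region?** Settings gives decile ranges of 7 to 10 (ACT), 3 to 7 (the Newcastle area) and 1 to 10 (Port Macquarie). A woman in decile 7 could live in any of the three. IRSAD may carry part of a regional difference, but it does not identify the region.

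**3. The plan's own figure.** Sample Size gives 578 per group for 36% versus 42%, two-sided 5%, 80% power. The usual formula gives

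n = [1.96·√(2·0.39·0.61) + 0.842·√(0.36·0.64 + 0.42·0.58)]² / 0.06² = (1.352 + 0.579)² / 0.0036 ≈ 1037 per group,

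and 578 per group gives about 55% power. This discrepancy is a separate issue. It matters here only because it explains why the power figures below start near 55%. Adding region changes no stated figure.

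**4. Cost of leaving region out.** The article gives no regional in-range rates, so these are assumed: 36% in the second region, with the first lower and the third higher by the gap shown. Region sizes are proportional to the births in Settings (5000, 5700, 2000), with about 1156 women, 1:1 allocation within region, a 6-point effect in every region, and 40,000 simulated trials per cell. A two-proportion test ignoring region is compared with a region-stratified Cochran-Mantel-Haenszel test.

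| Assumed gap | Type I, ignoring region | Type I, stratified | Power, ignoring region | Power, stratified |
|---|---|---|---|---|
| 0 | 4.8% | 4.8% | 55.4% | 55.4% |
| ±5 points | 5.0% | 5.1% | 55.7% | 55.8% |
| ±10 points | 4.6% | 4.8% | 56.4% | 57.5% |
| ±15 points | 4.3% | 4.9% | 57.3% | 59.1% |

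The largest power loss is 59.1 − 57.3 = 1.8 points.

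**5. Hand check of the last row.** Region weights are 5000/12700 = 0.394, 5700/12700 = 0.449 and 2000/12700 = 0.157, with rates 0.21, 0.36 and 0.51.

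- Overall rate: 0.394·0.21 + 0.449·0.36 + 0.157·0.51 ≈ 0.325
- Total variance: 0.325·0.675 ≈ 0.219
- Between-region variance: 0.394·0.115² + 0.449·0.035² + 0.157·0.185² ≈ 0.011, about 5% of the total
- True standard error relative to the one used: √(1 − 0.05) ≈ 0.97
- Effective critical value: 1.96/0.974 ≈ 2.01, so type I error ≈ 4.4%, in line with the simulated 4.3%

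A milder assumption of 30%, 36% and 42% in equal-sized regions gives 0.0024/0.230, about 1% of the variance.

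**6. What an arm-by-IRSAD estimate could show.**

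- As a ratio of relative risks per SD of IRSAD: SE = √(0.58/(0.42·578) + 0.64/(0.36·578)) = 0.074. The 95% CI spans a factor of exp(1.96·0.074) ≈ 1.16 either way. The trial's whole target effect is 42/36 = 1.17.
- As two equal IRSAD halves (289 women per arm in each, mean rate 39%): SE of the difference in risk differences = √(4·0.39·0.61/289) = 0.057. Power is 18% for a 6-point difference and 55% for 12 points. It reaches 80% only at about 16 points.

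**The case against.** The strongest reply is that nothing is at risk. Stratified allocation already balances region between the arms, so leaving it out of the model does not bias the comparison, and the calculation shows no inflation of type I error. That stands, and it sets the size of the point. Someone who sees a stratification factor left out might infer that the primary test is invalid. The documents do not support that, and under the assumptions above the error is in the safe direction.

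A reader might also take the Limitations section as evidence that weighing differs by region. It says: "The quality of the scales used and the procedures for maintaining and calibrating them may vary". The reference is to antenatal and birth care settings, not to the three regions, and it says only that variation is possible. Two of the regions contain two participating hospitals each, so a region term would not isolate differences between scales. Enrolment weight is in any case self-reported according to Data Collection. I give this sentence no weight.

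The third tempting reading is that the plan cannot answer its socioeconomic question. The formal aims, in the abstract and in Study Focus and Aims, concern engagement, acceptability and women's experience. They have their own method: focus groups arranged where possible by IRSAD, with a qualitative analysis within IRSAD groupings and then across them. The primary regression was not meant to serve them. What remains is the Discussion sentence, with some support from the Background of the abstract, which names effectiveness alongside acceptability as a gap. An interaction model could also properly sit in an analysis plan that is not shown, so its absence from the article is not in itself an error.

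The same defence does not cover region. The article chose to list its covariates, and the list departs from its own randomisation.

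**Conclusion.** The mismatch is real and its effect is small. Geographical setting is a randomisation stratum, it is absent from an explicit covariate list, and IRSAD does not stand in for it. The analysis as written stays valid, is slightly conservative, and gives up at most about 2 points of power if regional rates differ from 36% by up to 15 points. With gaps of 5 points or less the loss is negligible.

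These sizes rest on assumed regional rates, recruitment in proportion to births, and the same absolute effect in each region. The check compares simple tests rather than the planned covariate-adjusted regression. Because IRSAD would absorb some of any regional difference, the real loss may be smaller still.

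The IRSAD point is secondary: one claim in the Discussion goes beyond what the stated quantitative analysis can estimate. The aims themselves are not affected.

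**What to change.** Add geographical setting, coded at the three levels used in randomisation, to the primary regression alongside prepregnancy BMI. If it is deliberately left out, say why. Cost: two degrees of freedom and no new data, since region is known for every woman at randomisation.

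For the secondary point, choose one of two:

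- Prespecify one exploratory model with an arm-by-IRSAD term (continuous score), reported as a ratio of relative risks with its 95% CI, and state that power is low. Cost: one additional model.
- Reword the sentence in Principal Findings so that it matches the engagement and acceptability aims. Cost: an edit.

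Either change should be fixed before unblinded data are analysed.

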### Sample Size

This trial is designed to detect a clinically significant increase in the proportion of women who have a gestational weight gain within the current IOM recommendations from 36% to 42%. A recent prospective study in Australia with 664 participants (of all BMI categories) found that 36% of the cohort gained within the range recommended by the IOM [43]. This is greater than the proportion found in the LIMIT trial (33%), though this trial included only overweight and obese women [18] who are known to be more at risk of excessive weight gain. A total sample size of 1156 (578 in each group) will allow detection of statistical significance with 80% power and two-sided 5% significance level [44].

The follow-up period is short in studies using GWG as the primary outcome, given the end point is birth. However, there is wide variation in reported drop-out and loss to follow-up rates, which range from 3% to 20% [18,45-47]. These are composed largely of women experiencing miscarriage, fetal loss, and moving out of area. Taking a conservative approach, we have allowed for a 15% drop-out rate, which gives a total recruitment target of 1330 women.

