## Methods

### Study Design and Overview

This study is an unblinded, 2-armed randomized control trial that will test the primary hypothesis that a greater proportion of women in the intervention group compared with the control group will limit GWG within the range recommended by the IOM. We will randomize 1330 pregnant women to the control and intervention groups. Those in the control group will receive usual antenatal care, and those in the intervention group will receive usual care augmented with the smartphone app. Participants allocated to the intervention group are prompted by the smartphone app to discuss weight changes with their maternity or health care provider. The researcher responsible for analyzing the data will be blind to group allocation.

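### 578 women per group gives about 55% power for 36% versus 42%, not the 80% the protocol states

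*Protocol article*

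**What the plan says.** The primary outcome is binary (Data Collection): "the proportion of women whose GWG falls within the range recommended for them by the IOM for their baseline BMI". Allocation is individual and equal (Recruitment and Randomization): "Participants will be randomized using a 1:1 ratio in balanced blocks and stratified by BMI and geographical setting".

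The Sample Size section describes the effect to be detected as an increase in women with "gestational weight gain within the current IOM recommendations from 36% to 42" per cent, and calls it clinically significant. The control rate comes from an Australian cohort of 664 women that "found that 36% of the cohort gained within the range recommended by the IOM". The section then concludes: "A total sample size of 1156 (578 in each group) will allow detection of statistical significance with 80% power and two-sided 5% significance level".

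For losses it says: "we have allowed for a 15% drop-out rate, which gives a total recruitment target of 1330 women". Study Design and Overview repeats the target: "We will randomize 1330 pregnant women to the control and intervention groups".

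**The concern.** The section gives everything needed to recompute the sample size: two proportions, significance level, sidedness, power and, from the randomisation section, the ratio. A 6-point difference between proportions near 40% needs roughly 1,000 per group for 80% power, so 578 is far too small for the stated inputs.

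This calculation is the only justification given for recruiting 1,330 women. If the power is overstated, a null result would be read as coming from a trial with an 80% chance of finding a 6-point gain, when the real chance is little better than even. Under Results, the article reports about 100 recruits in roughly 12 months and says further funds are being sought, so the power statement may also inform decisions about continuing.

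**Working it through.** **Inputs, all from the protocol article**

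- p1 = 0.36, p2 = 0.42, difference d = 0.06, mean p̄ = 0.39 (Sample Size)
- two-sided α = 0.05, so z = 1.960; power 80%, so z = 0.842 (Sample Size)
- 578 per group, 1,156 in total (Sample Size); 1:1 allocation (Recruitment and Randomization)

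**Step 1. Try to reproduce 578 per group.**

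n = [1.960·√(2p̄(1−p̄)) + 0.842·√(p1(1−p1) + p2(1−p2))]² / d²

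- √(2 × 0.39 × 0.61) = 0.6898
- √(0.36 × 0.64 + 0.42 × 0.58) = 0.6885
- n = [1.960 × 0.6898 + 0.842 × 0.6885]² / 0.0036 = 1,036.2, so 1,037 per group

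The stated 578 is not reproduced. Variants of the method do not close the gap:

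| Method, 36% vs 42%, 80% power | n per group |
|---|---|
| Pooled variance under the null | 1,037 |
| Simple pooled, 2p̄(1−p̄) throughout | 1,037.4 |
| Unpooled variance | 1,033.4 |
| Arcsine | 1,036 |
| With continuity correction | 1,070 |
| One-sided 5% (contradicts the text) | 817 |
| Single-sample formula (wrong design) | 511 |
| One-sided 10% (contradicts the text) | 595 |
| **Stated** | **578** |

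The stated size is 578/1,036.2 = 56% of the requirement, a shortfall of about 458 women per group.

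**Step 2. Power at the stated size.**

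Power = Φ{[d − 1.960·√(2p̄(1−p̄)/n)] / √[(p1(1−p1) + p2(1−p2))/n]}

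At n = 578: (0.06 − 0.05623)/0.02864 = 0.1315, and Φ(0.1315) = 0.552.

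| Analysed per group | Basis | Power, two-sided 5% |
|---|---|---|
| 578 | as stated | 55.2% (unpooled 55.4%, arcsine 55.3%, continuity-corrected 52.8%) |
| 665 | all 1,330 analysed, no loss | 61.2% |
| about 565 | 1,330 × 0.85 = 1,130.5 in total | 54.3% |

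A one-sided test at 578 per group would still give only 67.3%.

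**Step 3. What 578 per group does support.**

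Holding the control rate at 36%, 80% power is reached at p2 = 0.4407, a difference of about 8.1 points. The number therefore fits an 8-point effect: 36% versus 44% needs 588 per group, and 34% versus 42% needs 577 (577.9, rounding to 578, by the simple pooled formula). A calculation run with 34% in place of 36% would explain the printed figure, but the article nowhere mentions 34%, so this remains an inference.

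**Step 4. Size needed for the stated target.**

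2 × 1,037 = 2,074 evaluable; 2,074/0.85 = 2,440 recruited at 15% loss.

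**The case against.** Nothing in the article restores 80%, but several points on the other side deserve an answer.

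- **The 55% depends on the printed rates.** If the calculation used 34% versus 42%, then 1,156 is right and a printed percentage is wrong. This stands as a caveat. However, the section gives 36% twice, once with a cited source, and contrasts it with 33% in another trial, so a simple misprint of the baseline cannot be assumed. Either way the section is wrong as printed.
- **The figures are for an unadjusted comparison.** Data Analysis plans regression adjusted for prepregnancy BMI, smoking, IRSAD score, parity and age, which may add some power. The article gives no figure for this and the sample size does not rely on it. As a rough approximation, an assumed 30% reduction in variance would raise power only to about 71%, and reaching 80% would take about 44%.
- **Multiple imputation and intention-to-treat.** These might make more of the 1,330 women count. The 61% figure already credits every randomised woman with complete information.
- **1,156 was meant per group.** That would give 84% power, but the text itself says 578 in each group.
- **The 565-per-group figure brings in another matter.** The target of 1,330 is 1,156 × 1.15, whereas allowing for 15% loss requires 1,156/0.85 = 1,360. That is a separate and minor point, and the main finding does not depend on it.
- **Slow recruitment may limit power more than the printed figure does.** That may be so, but it does not make the power statement correct.

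**Conclusion.** The point holds. On the protocol's own inputs, 578 women per group gives 55% power (53% to 55% across standard two-sided methods), not 80%. The chance of missing the target effect is about 45%, more than double the 20% implied. The stated target needs about 2,074 evaluable women, against 1,156 planned.

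This rests on the printed 36% and 42%, individual 1:1 allocation, a two-sided 5% test and an unadjusted comparison. No reading consistent with the text recovers 80%. What the article cannot settle is whether the error lies in a percentage or in the sample size.

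**What to change.** Go back to the original calculation first and establish which number is wrong. Then correct the Sample Size section so that rates, size and power agree:

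1. If 36% and 42% stand and the size is kept, state that 1,156 evaluable women give about 55% power for 36% to 42%, or that they give 80% power for 36% to about 44% (8 points). If the second form is used, it should be presented as what the size can detect. The article offers no support for 8 points as the clinically chosen difference.
2. If a printed rate is wrong, correct it, give its source and restate the difference.
3. If 80% power for 36% to 42% is to be kept, the target becomes about 2,440 recruited at 15% loss. At the reported recruitment rate this is a feasibility decision for the sponsor.

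Say that the figure is for an unadjusted comparison. Check any other place where the power claim appears, including the registry record, which was not available for this review; the article's abstract gives only the 1,330. Interpret a non-significant primary result by its confidence interval, not by reference to 80% power for 6 points.

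Options 1 and 2 are wording corrections, need no extra participants and can be made before results are known. The cost is that the stated design looks less favourable.
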